### Cluster randomisation

A CRCT is a randomised controlled trial in which groups of subjects (i.e., schools) are randomised rather than individual subjects (i.e., teachers) [48]. Cluster randomisation will be performed at the school level. This will provide the researchers with the opportunity to study the effects of an additional organisational health intervention that cannot be directed towards selected individuals (i.e., teachers) and to control for “contamination” across individuals (i.e., the effects on one teacher may influence the effects on another teacher in the same course) [49]. In the first secondary vocational school (known as an MBO in Dutch), participating teachers from one course (Care, Technology, or Economy) will be assigned to intervention group 1 (IG 1: MBSR), teachers from another course will be assigned to intervention group 2 (IG 2: MBSR and an additional organisational health intervention), and teachers from the third course will be assigned to the waiting list group (WG). The allocation will be different at each school (see Table 3). A researcher who is not involved in assigning courses/participants to the groups will prepare concealed, consecutively numbered, sealed opaque envelopes. Every envelope will contain a paper indicating the treatment assignment at school level (type 1, 2 or 3). The MBO schools will receive their envelopes from a researcher who is unaware of the randomisation sequence. The MBO schools can open the envelope in the presence of the researcher and the researcher will be informed about the treatment assignment.

**Table 3 Tab3:** Cluster randomisation

	Care	Technology	Economy
**MBO school, type 1**	IG 1^a^	IG 2^b^	WG^c^
**MBO school, type 2**	WG	IG 1	IG 2
**MBO school, type 3**	IG 2	WG	IG 1

^a^ IG 1: intervention group 1 (MBSR)

^b^ IG 2: intervention group 2 (MBSR and an additional organisational health intervention)

^c^ WG: waiting list group (control group that will receive MBSR one year later)

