### Procedures

All study participants will be asked to complete an online questionnaire on a secured website before the start of the intervention(s) (the starting date of the study is different for each school) (T_0_). After completing the questionnaire, the participating schools will be randomly assigned (type 1, 2, or 3; see Table 3), meaning that participants will take part in IG 1, IG 2, or WG depending on the course where they are working. At T_0_, the first author will conduct 10-min telephone interviews with at least 12 participants from IG 1 and 12 participants from IG 2 about their expectations of the interventions. All participants will receive the other three follow-up questionnaires on a secured website after the MBSR training (T_1_), 3 months later (T_2_), and 9 months after the MBSR training (T_3_). The first author will conduct face-to-face interviews with at least 12 participants from IG 1 and 12 participants from IG 2 at T_1_ and T_3._ At T_1_, some members of the participatory group that will be involved in the organisational health intervention - excluding the teachers participating in IG 2 (e.g., a superior, an HR consultant, and the director of the programme) - will be interviewed about the process and effects of the organisational health intervention.

Participants in IG 1 and IG 2 should attend at least four of the nine MBSR sessions, because Bear et al. [50] revealed that structural changes in perceived stress did not occur until after four MBSR sessions [19]. Participants in WG will attend a MBSR programme one year later.

The collected data will be stored on a secure disk to ensure confidentiality. Not the researcher (MJ) but an independent external organisation, assigning encrypted numbers to the participants, will collect the data. The researcher (MJ) cannot link the numbers and the participants. Only the researcher (MJ), the members of the project management group and a methodologist (HK) will have access to the data.

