### Statistical analyses

Baseline characteristics of participants will be presented as means and standard deviations (SDs) for metric variables, and as frequencies and percentages for categorical variables. The outcomes of the questionnaires will be compared at baseline (T_0_), immediately after the intervention(s) (T_1_), 3 months later (T_2_), and 9 months after the intervention(s) (T_3_). All analyses will be conducted according to the intention-to-treat (ITT) principle. ITT analysis, based on the initial treatment allocation and not on the treatment eventually received, will avoid the effects of drop-out, and as such we prevent breaking the random allocation to the intervention groups [79]. Per-protocol (PP) analyses in the treatment-adherent sample (i.e., participants in IG 1 and IG 2 have to attend at least four of the nine MBSR sessions, and participants in WG cannot attend a MBSR programme or stress reduction training) will also be performed. The aim of PP analysis is to assess the effects of MBSR and the additional organisational health intervention *under optimal conditions***:** what is the effect if participants are fully compliant [80]? Therefore, drop-outs need to be excluded from any PP analysis.

The quantitative short-term and long-term effects of MBSR and the additional organisational health intervention (differences between T_0,_ T_1_, T_2_, and T_3_) will be examined using longitudinal regression analysis (generalised estimating equations, GEE, or mixed models), which is fit to analyse longitudinal/clustered data in clinical trials [81] or repeated-measures designs (general linear model, GLM) [82]. The baseline values of outcomes (T_0_) of the three groups (IG 1; IG 2; WG) will be defined as independent variables, while the outcomes on the follow-up measurements (T_1_, T_2_, T_3_) will be treated as dependent variables. Correction of confounding variables will be applied.

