The proposed study will use a mixed-methods approach, which is rare in studies on the effects of MBSR [19]. That approach means that, in addition to quantitative data, qualitative data will be collected to investigate in-depth relevant process measures and to capture the mechanisms by which MBSR (key aspects of the MBSR programme) and the organisational health intervention (factors for successful implementation in an organisation) result in specific outcomes. Another strength of the proposed study is the integrated approach, which combines an individual-focused secondary intervention (MBSR) and an organisation-based primary intervention. This is important since teachers’ stress likely results from a complex interaction between personal characteristics of the teacher and the environment (work and personal circumstances) [6, 84].

The design of the cluster randomised controlled trial (CRCT), in which schools are randomised as opposed to individual teachers, is another strength of our proposed approach. CRCT allows us to study the effects of an organisational health intervention and to control for “contamination” across participants [48, 49].

Despite the many strengths of the proposed study, complying with research ethics implies that we cannot account for some limitations that have already been raised in previous literature. For example, the proposed study design will be based on self-selection, as we depend on voluntary participation by teachers, which may result in somewhat biased samples. Moreover, it is likely that the characteristics of the teachers who participate in the proposed study (e.g., motivation, sensitivity to the MBSR training and the organisational health intervention, personality) may differ from those who will not participate or those who drop out early.

We assume that many participants experience work pressure, time pressure, and stress complaints. The MBSR training (and the additional organisational participatory health intervention) requires a lot of time and effort from the teachers. We are therefore aware that (potential) participants have to be motivated to prevent premature drop-out.

In line with this, the time frame of the organisational health intervention (8–12 weeks) is a short period with regards to capturing organisational changes. Therefore, the T_1_ measurement might occur too soon to detect effects. However, the measurements at T_2_ and T_3_ overcome this limitation.

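### The protocol names the school as the cluster, but the course within a school carries the arm, and the permitted analyses can leave that level out and overstate precision

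*Protocol article*

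**What the plan says.** The Cluster randomisation section defines the design as one where "groups of subjects (i.e., schools) are randomised rather than individual subjects (i.e., teachers") and adds "Cluster randomisation will be performed at the school level". The Discussion lists as a strength a design "in which schools are randomised as opposed to individual teachers".

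The same section then describes the allocation inside one school: "participating teachers from one course (Care, Technology, or Economy) will be assigned to intervention group 1", "teachers from another course will be assigned to intervention group 2", and the third course goes to the waiting list. On the envelopes it says: "Every envelope will contain a paper indicating the treatment assignment at school level (type 1, 2 or 3"). Each type is one row of Table 3, and each row holds IG 1, IG 2 and WG once. The Procedures section confirms that "participants will take part in IG 1, IG 2, or WG depending on the course where they are working".

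The Statistical analyses section offers GEE or mixed models, described as suited to longitudinal or clustered data, "or repeated-measures designs (general linear model, GLM"). It says that confounders will be corrected for. It does not say at which level clustering will be modelled.

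**The concern.** A cluster trial has to be analysed at the level that carries the treatment. If that level is named wrongly, an analyst who follows the text may enter school as the grouping factor. Because all arms sit in every school, a school effect cancels from the arm contrast. Variation between courses within a school does not cancel. It stays in the contrast but is missing from the standard error.

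The other permitted routes share the gap. A repeated-measures GLM, or a GEE or mixed model grouped only on the teacher, handles correlation over time within a teacher but not correlation between teachers of the same course.

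Some such correlation is plausible by design. MBSR is taught in groups of 4–15 by one of four trainers, the organisational intervention is aimed at a whole course, and the protocol itself places contamination between teachers of the same course. At stake are the confidence intervals and p-values of the arm comparisons.

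**Working it through.** **1. Unit carrying the arm.** Table 3 is a 3 × 3 Latin square with school type as row, course as column and arm as cell. Arm varies within school, so school is a block. With three schools there are 9 course-within-school cells, 3 per arm. With 22 teachers per arm (Sample size section), the mean cell size is 22/3 = 7.33, for example cells of 8, 7 and 7.

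**2. The plan's own figure.** Repeated-measures ANOVA, group-by-time interaction, f = d/2 = 0.25, 3 groups, m = 2 measurements, correlation 0.5 (assumed; not stated): λ = f²·N·m/(1 − 0.5) = 0.0625 × 66 × 2/0.5 = 16.5 on 2 and 63 df. Power is 0.9535, so N = 66 is reproduced. This calculation treats teachers as independent and has no cluster term.

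**3. Standard error.** Take total variance 1 for one baseline-adjusted follow-up score, a school share ρs and a course-within-school share ρc. Both are assumptions, because the protocol gives no ICC.

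- For cells of 8, 7 and 7, Σn²/22² = 162/484 = 0.335. The variance of an arm difference is about 2[0.335ρc + (1 − ρc − ρs)/22].
- At ρc = 0.10 and ρs = 0.05 this is 2[0.0335 + 0.0386] = 0.144, an SD of 0.380 (simulated: 0.385).
- The mean model SE is 0.293 with no cluster term and 0.284 with a school effect. The ratios to 0.385 are 0.761 and 0.738, so the SE is 24–26% too small.
- The critical value 2.00 shrinks in effect to 1.52 and 1.48, giving two-sided error of about 12.8% and 14.0%.

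**4. Simulated type I error.** IG 1 against WG at nominal 5%, N = 66, three schools, ρs = 0.05, 4,000 runs per setting (Monte Carlo SE at 5% = √(0.05 × 0.95/4000) = 0.34 points):

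| ρc | no cluster term | school effect only | 9 cell means, school as block (4 df) |
|---|---|---|---|
| 0 | 5.3% | 5.3% | 5.1% |
| 0.01 | 5.1% | 5.5% | 4.7% |
| 0.02 | 6.4% | 6.8% | 4.8% |
| 0.05 | 8.5% | 9.3% | 5.8% |
| 0.10 | 13.2% | 14.1% | 5.3% |
| 0.20 | 21.4% | 23.1% | 5.3% |

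A separate simulation with baseline correlation 0.5 gave 6.7 / 8.8 / 13.0% (no cluster term) and 6.7 / 9.0 / 13.4% (school effect) at ρc = 0.02 / 0.05 / 0.10. A third gave about 6 / 9 / 12% and 7 / 10 / 13%.

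**5. Where the inflation starts.** With no cluster term, the SE is too small only if (7.33 − 1)ρc > ρs. That means ρc above 0.05/6.33 = 0.008 when ρs = 0.05, or above 0.20/6.33 = 0.032 when ρs = 0.20. Below that the test is neutral or slightly conservative.

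**6. Robust GEE.** Clustered on three schools, the error is about 25% even at ρc = 0. Analytically it is 2·P(t₂ > 1.96·√(2/3)) = 0.251. It falls to about 10% with 10 schools and about 5% with 40. Clustered on the nine cells without a small-sample correction, it is about 7–19%.

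**7. Degrees of freedom for cell means.** 9 − 1 − 2 (school) − 2 (arm) = 4. Adding course leaves 2.

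**The case against.** The sentence about randomising at school level is literally true, since one envelope per school holds one row of the table. The course mapping is set out openly. That stands: the fault is treating the school as the unit that bears the treatment, not a misreported draw.

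A reader might infer that the protocol commits to an analysis by school. It does not. The level is left open, and a mixed model with a course-within-school effect fits the text. Random-effects structure and degrees of freedom often belong in an analysis plan, which is not shown. What remains is on the page: a wrong label for the cluster, and a GLM offered as an equal alternative.

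A reader might also infer that GEE clustered on school is wrong in principle. It is not, because school contains course. It fails here because there are only three schools.

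Nor does leaving out course bias the arm contrast. Types are assigned to schools at random, so an extra school brings chance imbalance only, and the planned correction for confounders permits course adjustment.

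Finally, one might argue that three schools allow only six allocations and hence a p-value floor of 1/6. The plan proposes no randomisation test, and three is the minimum number of schools, so this does not follow.

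**Conclusion.** The point holds as a conditional one. The document names the school as the cluster although every school contains all three arms, and it permits analyses without a course-within-school effect. At the planned size, a nominal 5% pairwise test then runs at about 6–7%, 9% and 12–13% for a course-within-school ICC of 0.02, 0.05 and 0.10. A school effect does not repair this (7%, 9–10% and 13–14%).

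These figures rest on an assumed ICC in the baseline-adjusted score, three schools, and cells of seven or eight teachers. At an ICC of 0.01 or below the error is near nominal. It is therefore not supported to say that the p-value of every outcome is too small: the protocol gives no ICC for any of its many scales, and they may differ.

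**What to change.** State in the Cluster randomisation section and the Discussion that schools are blocks, each drawing one row of Table 3, and that the cluster is the course within a school. In the Statistical analyses section, remove the repeated-measures GLM and any GEE or mixed model without a course-within-school term. Specify one model:

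- fixed effects for arm, time, arm-by-time and the baseline value, with school as a design factor;
- a random intercept for each course-within-school cell;
- correlation over time within teacher;
- small-sample degrees of freedom, such as Satterthwaite.

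An analysis of cell means with school as block is an acceptable equivalent (4 df with three schools). Adjusting for course as well is optional. It costs 2 of those 4 df and raises the critical t from 2.78 to 4.30.

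No new data are needed: course is a recorded baseline item and school is known from the allocation. The cost is wider intervals on few degrees of freedom. For a difference of 0.5 SD with ρs = 0.05, the cell-means test has simulated power of 26%, 21% and 17% at ρc = 0, 0.05 and 0.10. The test without a cluster term has 38% at ρc = 0, where it is valid.

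The cell variance will also often be estimated as zero. With cells of 7 the chance is P(F₄,₅₄ < 1/[1 + 7ρc/(1 − ρc)]), about 59% at ρc = 0 and 31% at 0.10. The plan should say in advance what is done then. Estimates and intervals, not p-values, should lead the report.

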**Methods:**

The proposed study comprises a cluster randomised controlled trial that will be conducted in at least three secondary vocational schools, to which teachers will be recruited from three types of courses: Care, Technology, and Economy. The allocation of the intervention programme to the participating schools will be randomised. The teachers from each school will be assigned to intervention group 1 (IG 1), intervention group 2 (IG 2), or the waiting list group (WG). IG 1 will receive MBSR training and IG 2 will receive MBSR training combined with an additional organisational health intervention. WG, that is the control group, will receive MBSR training one year later. The primary outcome variable of the proposed study is mindfulness, which will be measured using the Dutch version of the Five Facet Mindfulness Questionnaire (FFMQ-NL). In the conceptual model, the effects of teachers’ mindfulness resulting from the intervention programmes (MBSR training and MBSR training combined with an additional organisational health intervention) will be related to salient (secondary outcome) variables: mental health outcomes (e.g., burnout, work engagement), work performance, work-related perceptions (job demands and job resources), and personal competencies (e.g., occupational self-efficacy). Data will be collected before (T_0_) and immediately after the MBSR training (T_1_), and 3 (T_2_) and 9 months (T_3_) after the training. The power analysis revealed a required sample size of 66 teachers (22 in each group).

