### Participants and recruitment

Study participants will be recruited from the teaching staff at no fewer than three secondary vocational schools. When a secondary vocational school agrees to participate, we will recruit potential participants from three programmes (Care, Technology, and Economy) using e-mail, posters, flyers, and each school’s intranet. The researchers, Human Resources (HR) consultants, and supervisors will inform potential participants about the research project.

Respondents who are willing to participate will be screened in terms of the eligibility criteria by the first author (MJ) (see Table 2). Eligible candidates will receive an information letter about the project. This letter includes the information as approved by the ECPR and the METC and the informed consent letter. One week before the start of the interventions, cluster randomisation will be conducted and the participants will be informed about their assignment to one of the intervention groups or the waiting list group.

**Table 2 Tab2:** Eligibility criteria

Inclusion criteria	Exclusion criteria
Teachers in the Care, Technology, and Economy courses	Attended mindfulness training in the past 2 years
Employed in a secondary vocational school for at least 2.5 days a week for at least 1 year	Attended stress reduction training (e.g., cognitive therapy or relaxation training) in the past 2 years

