### Interventions

#### MBSR: main intervention

MBSR, developed by Kabat-Zinn [51], is the most common form of secular mindfulness-based training [52]. MBSR aims to reduce suffering or stress [53] and was originally developed for patients with chronic pain. This training programme is primarily based on Kabat-Zinn’s curriculum [51], but it contains elements of mindfulness-based cognitive therapy (MBCT) [54]: in particular, a 3-min breathing space and psycho-education about the nature of thoughts. The MBSR programme will consist of eight 2.5-h weekly group sessions, each with 4–15 participants per group, homework involving 45 min of daily home exercise 6 days a week, and one day with 7-h of silence. The sessions will be supervised by one of the four recruited, qualified, mindfulness trainers, who will receive a training script. The first session will begin with a short introduction to the programme and meet and greet between participants. Each session will consist of different meditation exercises, enquiry, psycho-education, and a specific theme (see Table 4). At the end of each session, participants will be given homework that will be discussed in the subsequent session.

**Table 4 Tab4:** Content of MBSR group sessions

Session	Theme	Content of group sessions	Homework
1	Automatic pilot	• Introduction • Raisin-eating exercise • Body scan	• Body scan • Attention to routine activity • Eating one meal mindfully
2	Perceiving clearly	• Body scan • Imagery exercise to demonstrate the relationship between thoughts and feelings • Sitting meditation, paying attention to breathing	• Body scan • Attention to breath • Awareness of pleasant events • Attention to routine activity
3	From doing to being: a mode of doing and a mode of being	• Lying-down yoga exercises • Sitting meditation with a focus on breathing, bodily sensations, sounds • Pleasant events • Seeing exercise to demonstrate the difference between observation and interpretation • Three-minute breathing space (mini-meditation)	• Body scan • Lying-down yoga exercises • Attention to breath • Awareness of unpleasant events

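### Three allocation types cannot differ across four or more schools, and course balance between arms rests on equal numbers per type while no course or school term is named

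*Protocol article*

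**What the plan says.** **Number of schools.** Participants and recruitment states that "Study participants will be recruited from the teaching staff at no fewer than three secondary vocational schools". The abstract likewise has the trial "conducted in at least three secondary vocational schools". No upper limit is given.

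**Allocation.** Within a school, each of the three courses goes to a different arm. The Cluster randomisation section then says "The allocation will be different at each school (see Table 3". Table 3 lists three patterns, and of the envelopes the same section says: "Every envelope will contain a paper indicating the treatment assignment at school level (type 1, 2 or 3". Procedures repeats that "the participating schools will be randomly assigned (type 1, 2, or 3; see Table 3". Neither section says whether types are drawn with or without replacement, or what happens after the third school.

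**Analysis.** The Statistical analyses section offers GEE, mixed models or a repeated-measures general linear model. It says "The baseline values of outcomes (T_0_) of the three groups (IG 1; IG 2; WG) will be defined as independent variables", and adds "Correction of confounding variables will be applied" without listing the variables. Course is among the recorded baseline characteristics.

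**The concern.** Table 3 is a Latin square of type by course. Every course meets every arm once, so each arm has the same course mix, provided each type covers the same number of teachers. The document secures neither condition. The number of schools is open upwards, and teachers volunteer, so school sizes are whatever recruitment yields. A fourth school breaks the square and also makes the stated rule impossible to follow.

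Once the square is unbalanced, each arm leans towards a different course. If teachers in one course change differently over the year from those in another, for reasons unrelated to training, part of that difference appears in the arm contrasts. Adjusting for the T0 score removes differences in level but not differences in change. Course is the factor by which arms are allocated within a school, so whether to adjust for it should not be left to a judgement about confounding made after the data are seen.

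**Working it through.** **The plan's own figure.** The total of 66 (3 x 22) reproduces as the group-by-time test of a repeated-measures ANOVA: f = d/2 = 0.25, 3 groups, 2 measurements, noncentrality f² x N x m/(1 - rho), df 2 and N - 3. With rho = 0.5 (assumed; the article gives none), power is 0.9535 at N = 66 and 0.9436 at N = 63. The point here does not depend on this figure; it only supplies the scale (22 per arm, target d = 0.50).

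**Step 1: can every school differ?** Three types serve at most three distinct schools, so with four schools the chance that all differ is 0. If types were drawn independently, even three schools would all differ only 6/27 = 22% of the time. Three arms over three courses have 3! = 6 arrangements, so the limit comes from Table 3 and not from the design.

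**Step 2: course mix by arm, from Table 3.**

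| Layout | IG 1 Care / Tech / Econ | WG Care / Tech / Econ |
|---|---|---|
| 3 equal schools, each type once | 33 / 33 / 33% | 33 / 33 / 33% |
| 4 equal schools, type 1 repeated | 50 / 25 / 25% | 25 / 25 / 50% |
| 12, 6, 4 teachers per course on types 1, 2, 3 | 55 / 27 / 18% | 27 / 18 / 55% |
| 6 equal schools, each type twice | 33 / 33 / 33% | 33 / 33 / 33% |

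The 12/6/4 layout is illustrative. It gives 22 per arm, 66 in total. Its cells also fit the training groups, "each with 4–15 participants per group", although that range describes MBSR groups and sets no limit on school-by-course cells.

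**Step 3: shift in an unadjusted contrast.** Let g be the Care minus Economy difference in baseline-adjusted follow-up, with Technology midway (assumed). Each arm's expected offset, relative to Economy, is g x (Care share + 0.5 x Technology share).

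- IG 1: (12 + 0.5 x 6)/22 = 0.682
- WG: (6 + 0.5 x 4)/22 = 0.364
- IG 2 (Technology 12, Economy 6, Care 4): (4 + 0.5 x 12)/22 = 0.455

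IG 1 minus WG is therefore shifted by 0.318g, IG 2 minus WG by 0.091g, and IG 1 minus IG 2 by 0.227g. For assumed g of 0.3, 0.5 and 0.8 SD, 0.318g is 0.10, 0.16 and 0.25 SD.

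**Step 4: all six assignments of the types to the 12/6/4 schools.** IG 1 minus WG is +0.318g, -0.091g or -0.227g, twice each. The mean is (0.318 - 0.091 - 0.227)/3 = 0. In every assignment exactly one of the three arm contrasts has an absolute shift of 0.318g; which one depends on the draw.

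**Step 5: milder inequality and four schools.**

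- 10/7/5: largest shift 0.18g (0.05 to 0.15 SD for g of 0.3 to 0.8).
- 8/7/7: about 0.05g (0.01 to 0.04 SD).
- Four equal schools with one type repeated: 0.25g for the most affected contrast.
- Four schools of 6/6/5/5 with both larger schools on one type: 0.318g.

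**Step 6: effect of adjusting.** By individual-level least squares with residual SD 1, the standard error of an arm contrast in 12/6/4 is sqrt(2/22) = 0.302 unadjusted. With course fitted it is 0.319 (about 6% larger) and the shift is exactly zero. Adding school leaves 0.319. School alone does not remove the shift. In 6/6/5/5 the adjusted standard error is 0.318.

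**Step 7: cell-level degrees of freedom, three schools.** Nine school-by-course cells leave 9 - 3 = 6 with arm alone, 4 with course added, and 2 with course and fixed school. The two-sided 5% critical t is 2.45 with 6 df and 4.30 with 2.

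**The case against.** **The model may well include course.** A reader might infer that the analysis has no course or school term. The text does not support that. It names none, but the confounder clause is open, the chosen methods suit clustered data, and a covariate list is commonly left to an analysis plan that is not shown. What stands is narrower: the article fixes adjustment only through a confounding clause, although course is part of how treatment is allocated.

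**The shift is not systematic bias.** A reader might take the course imbalance as bias built into the design. Types are assigned to schools at random, and Step 4 shows a mean of exactly zero. This objection stands in full. What remains is that as few as three schools are randomised once, and a model without course does not correct the imbalance that this single draw produces.

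**The example is unfavourable.** 12/6/4 is a strongly unequal layout, and quoting only IG 1 minus WG with the largest school on type 1 would pick the worst draw for that contrast. Step 4 answers the second part, since some contrast carries 0.318g under every draw. The first part stands: near-equal schools give a negligible shift. For 6/6/5/5, 0.318g needs both larger schools on the same type, which is uncommon. The course differences are assumptions throughout.

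**School is surely known.** A reader might infer from its absence among the baseline characteristics that school is not recorded. That list describes participants. School is the randomised unit with its own envelope and start date, so its absence there shows nothing.

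**Fixed school effects are costly.** This stands for three schools: with course they leave 2 cell-level degrees of freedom, and the least-squares standard errors above ignore clustering. It argues against insisting on fixed school effects, not against naming course.

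**Conclusion.** The point holds in two parts. First, the text contradicts itself: more than three schools are permitted, each is to have a different allocation, and only three types exist. No reading of Table 3 resolves this for a fourth school. Second, balance of course over the arms depends on equal numbers per type, which nothing secures, and the named model terms do not include the factor by which arms are allocated.

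The size of the second part is conditional. It is a realised chance imbalance, zero on average, and matters only if courses differ in baseline-adjusted follow-up, which the documents do not quantify. Under the stated assumptions the most affected contrast is shifted by 0.01 to 0.04 SD in 8/7/7, 0.05 to 0.15 SD in 10/7/5 and 0.10 to 0.25 SD in 12/6/4. The upper end is about half the target effect of 0.50. Nothing here invalidates the trial; the remedy is cheap and worth making.

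**What to change.** **Analysis.** Name course (Care, Technology, Economy) as a fixed factor in every outcome model, whatever the baseline comparison shows. Carry school as a field in the coded data set and account for it as a fixed or random term, stating which.

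**Allocation.** State that types are drawn without replacement in full sets of three, with a fresh set for schools beyond the third. Replace the claim of a different allocation at each school with a different allocation within each set of three. By the article's own dates (first assignments September 2016, last assessments June 2020) allocation is probably complete; if so, report the rule actually used and the number of schools on each type.

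**Cost.** Wording, plus a standard error up to about 6% larger in the unequal examples. For three schools, cell-level degrees of freedom fall from 6 to 4 with course, and to 2 if school is also fixed. A full set of three makes the last type in each set predictable once two are known, and an incomplete second set still leaves some imbalance, which the course term then handles.
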